### Study location

The study will be carried out in the rooming-in wards of the hospitals: Clinics of the Federal University of Triangle Mineiro (HC-UFTM), in Uberaba (MG); Inacia Pinto dos Santos (HIPS), in Feira de Santana (BA) and at the Maternity School of the Federal University of Rio de Janeiro, in Rio de Janeiro (RJ).

In context, the Clinics of the Federal University of Triangle Mineiro (HC-UFTM) recorded 1259 deliveries in 2020. Reference for the resolution of high-risk pregnancies, infectious diseases in the pregnancy-puerperal cycle, for patients assisted in pathological prenatal care in municipalities in the Southern Triangle of Minas Gerais, and for pregnancies at usual risk located in the region of the institution and in all cities in the Southern Triangle of Minas Gerais that do not have a hospital. It is a public hospital with 100% of its services linked to the Unified Health System (SUS). It has 12 rooming-in beds and does not have the title of Baby-Friendly Hospital.

The Hospital Inacia Pinto dos Santos (HIPS) is characterized by being the first hospital in Bahia to receive the title of Baby-Friendly Hospital and being a reference in caring for women and newborns at normal risk. A public teaching hospital with three rooming-in units recorded 7501 deliveries in 2022 and has an installed capacity of 95 beds.

At the Maternity School of the Federal University of Rio de Janeiro, in 2020, 1607 births were recorded. Also characterized by public assistance and as a teaching hospital, its AC has nine wards totaling 45 active beds. Pregnant women of normal risk and those who need treatment for intercurrent illnesses or those related to pregnancy are assisted. The institution received the title of Baby-Friendly Hospital in December 2020.

### Inclusion and exclusion criteria for participants

Will be included in the study, primiparous, aged over 18 years; who were pregnant with a single fetus, with live birth, gestational age of 37 to 42 weeks, birth weight greater than 2500 g, regardless of the type of delivery; who are hemodynamically stable, conscious, and oriented and admitted to the rooming-in wards, of the participating centers, at the time of allocation for the study.

Postpartum women and newborns with contraindications for breastfeeding (HIV positive; HTLV 1 and 2 positive or neoplastic treatment with chemotherapy) will not be included; infants with malformations that prevent or make breastfeeding difficult or with changes in breastfeeding mechanics (lingual frenulum); puerperal women whose infants were immediately separated after clamping the umbilical cord at birth due to maternal-neonatal complications, in which one or both were hospitalized in critical units; postpartum women transferred from other institutions or who have already been discharged (rehospitalization), postpartum women using illicit drugs, postpartum women with intellectual or sensory disabilities with a medical diagnosis. These criteria contemplate the feasibility of the intervention and the necessary follow-up to the clinical trial.

Women who are not followed up in the first month, after three unsuccessful attempts at contact and at least one contact with a family member at different times, will also be excluded if malformations or abnormalities in the mechanics of breastfeeding or changes in the mother–child bond are detected at the time of allocation.

### Randomization, concealment of allocation, and masking

The sample will be probabilistic and calculated after conducting a pilot test with 60 postpartum women (20 in each center). A significance level of 5% and a statistical power of 95% will be considered. The postpartum women will be recruited by the research team, duly qualified for this action, and allocated through randomization by blocks composed of eight participants in two groups: intervention and control.

The randomization lists of each research center will be organized by a central of randomization, which will manage the allocation groups. This list will be prepared using the Randon® program. The researchers will contact the members of the randomization center to consult the order of inclusion of postpartum women in the research and their allocation group. This center will carry out allocation concealment, which will not be directly involved in the study data collection. There will be no blinding of participants and researchers involved in the collection.

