### Study design

This is a multicenter, randomized, superiority, parallel, and open clinical trial guided by the international recommendations of the Consolidated Standards of Reporting Trials [14].

The randomized clinical trial is considered the gold standard for evaluating health interventions, establishing a causal relationship, and evaluating the effectiveness of the intervention [15].

This is a superiority study, because it will determine whether the investigational intervention is superior to the comparator; parallel study, as each group of participants will be exposed to only one intervention studied (intervention or control); random, as participants will be allocated between groups, and each individual has the same probability of being selected for one group or another [16, 17]; and open, as there will be no masking of the intervention (participants and researchers) [18–21], because it would be impossible to blind this intervention for women and nurses. However, data analysis will be carried out by researchers not directly involved in data collection.

This clinical trial protocol was designed following the Standard Protocol Items: Recommendations for Interventional Trials (SPIRIT) [22] as evidenced in the checklist (see Additional File 1).

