### Recruitment and data collection procedures

The researcher, daily, will go to the nurses responsible for the ward and locate the census of hospitalized puerperal women and identify the primiparous women who delivered at term and the bed in which they are hospitalized. The following information will be checked in the medical records: HIV and HTLV 1 and 2 serological test results; information on neoplastic diseases currently being treated with chemotherapy; neonatal malformations; diagnosis of neonatal ankyloglossia; description of separation at birth (hospitalization in critical units—women or newborn); readmission due to maternal or neonatal complications; illicit drug users; postpartum women with a medical diagnosis of intellectual difficulty or sensory deficit. If it has any of the present criteria, it will not be included in the list for randomization. If there are no criteria for non-inclusion, randomization will be performed. The gestational age and birth weight of neonates will also be checked.

Once the criteria are met, the researcher will go to the ward, explain the study’s objectives to the selected postpartum women and read the Informed Consent Form (ICF). When deciding positively to participate, the postpartum woman must sign the ICF in two copies, receiving a copy and another that the researchers will keep. The researcher will contact the randomization center, and eligible postpartum women will be randomized to the control or intervention group as directed by the center.

In the control group, the interview, evaluation of the breasts, and at least one feeding will be performed using the abovementioned instruments. At the end (zero time), the researcher will reinforce the telephone contacts and offer the videoscribe visualization. Unfilled information can be extracted from the medical records, and the care complexity scale will be filled in.

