In the intervention group, the postpartum woman will be approached with the strategy of counseling, breast evaluation, and at least one breastfeeding and interview according to a validated protocol. Ultimately, the researcher will reinforce the subsequent contacts, which will succeed in the allocation, interspersed in the morning and afternoon, depending on time zero, until hospital discharge. In the follow-up at the hospital, an approach with a counseling strategy will be carried out, identifying doubts and potential needs. In the end, the videoscribe will be offered and reinforced about subsequent telephone contacts for follow-up and their importance.

To characterize the sampling, the researcher will complete a daily list of eligible postpartum women, included or not included, and reasons for non-inclusion.

If the researcher detects abnormalities in the mechanics of breastfeeding or changes in the mother–child bond, the care team members will be notified, and the participant must be excluded.

Follow-up interviews will be done through phone calls. The researcher will make three telephone contact attempts at different times of the day: between 12:30 pm and 1:30 pm, from 4:00 pm to 5:00 pm, or at another preferred time indicated by the participant. If the attempt is unsuccessful, the researcher will try to contact the number provided by the family member. If accepted, the researcher will apply the questionnaire, thank them, and inform a new contact within a week. Contact will be made by the researcher who collected the data with the postpartum women included to maintain the link with the postpartum women and reduce sample losses.

In the second week, the same procedures will be carried out, but at the end, the researcher will signal a new contact in 2 weeks; in the first month, he will inform that he will return in 3 months, and on the fourth month, he will inform that the next call will be in 2 months. At the end of the protocol, the researcher will close the research and thank the participant.

Postpartum women who are not followed up in the first 15 days, after three unsuccessful contact attempts and at least one contact with a family member at different times, will be excluded.

All data will be completed in Google Forms® electronic forms on tablets purchased for this purpose. Only researchers will have access to the electronic database, collection instruments, and consent forms.

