### Statistical methods

#### Sample size

The sample size will be calculated by a statistician with no clinical involvement in the research and obtained after carrying out the pilot study.

Previously, a pilot study will be conducted with 60 participants being recruited, 20 participants from each center, 10 allocated in the intervention group, and 10 in the control group for each center. To achieve a high confidence level for a pilot study, a minimum sample of 50 research subjects is recommended [36]. A significance level of 5% and a statistical power of 95% will be considered, and the sample calculation will be performed after analyzing the pilot study, as well as follow-up losses will be considered, using the OpenEpi version 3.01 program.

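### A single published block size of eight in an open trial lets a recruiter who tracks allocations foresee up to one in five with certainty

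*Protocol article*

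**What the plan says.** The Protocol article states one block size, in the Methods part of the abstract and again under Randomization, concealment of allocation, and masking: "allocated through randomization by blocks composed of eight participants in two groups: intervention and control". Neither place mentions varying sizes or keeping the size from recruiting staff. The lists are separate by centre: "The randomization lists of each research center will be organized by a central of randomization". That central unit conceals the allocation and is not directly involved in data collection.

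The trial is open: "There will be no blinding of participants and researchers involved in the collection". Under Recruitment and data collection procedures, the researcher screens the ward each day, checks eligibility in the records, explains the study, obtains signed consent and only then requests the arm: "The researcher will contact the randomization center, and eligible postpartum women will be randomized to the control or intervention group as directed by the center". The follow-up calls fall to the same person: "Contact will be made by the researcher who collected the data with the postpartum women included".

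The ratio within a block is not written out. Equal allocation follows from Study design ("each individual has the same probability of being selected for one group or another") and from the pilot split under Sample size.

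**The concern.** Concealment has two parts: nobody can see the list, and nobody can work out its next entry. The protocol secures the first. The second fails towards the end of a block when the block size is fixed and known and earlier allocations are visible. Here the size is printed in a public article, and the person who approaches the next woman has learned the arm of the women she enrolled before.

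Once four women in a block have gone to one arm, the rest of that block must go to the other. A recruiter who knows this can be influenced, knowingly or not, in whom to approach, when, and how the study is presented at consent. The primary outcome is the duration of exclusive breastfeeding. It plausibly depends on motivation and early feeding, which a recruiter can observe at the bedside. Adjustment can address measured differences that arise this way, but not unmeasured ones such as motivation.

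**Working it through.** The article gives no figure for predictability and no sample size for the main trial, so there is nothing to reproduce. The results are shares, not counts of women.

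**Inputs**
- Block size 8, one list per centre (Randomization section).
- Four places per arm in each block (inferred from Study design and Sample size).
- The observer knows the block size and every earlier allocation at the centre (an assumption: the article gives neither the number of recruiters per centre nor whether they share a log).

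**Certain allocations with fixed blocks of eight**

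There are C(8,4) = 70 equally likely blocks. An allocation is certain when the other arm's four places are already used, so the number of certain allocations is the length k of the final run of one arm. The number of blocks with a final run of exactly k is 2 × C(7−k, 3):

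| k | Blocks | Share |
|---|---|---|
| 1 | 2 × C(6,3) = 40 | 57.1% |
| 2 | 2 × C(5,3) = 20 | 28.6% |
| 3 | 2 × C(4,3) = 8 | 11.4% |
| 4 | 2 × C(3,3) = 2 | 2.9% |

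Mean = (1×40 + 2×20 + 3×8 + 4×2)/70 = 112/70 = 1.6 per block, and 1.6/8 = 20%. The general form for a block of 2m is a share of 1/(m+1), here 1/5.

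By position, the chance that the allocation is certain is 0 for the first to fourth, 2/70 = 2.9% for the fifth, 10/70 = 14.3% for the sixth, 30/70 = 42.9% for the seventh and 100% for the eighth. These sum to 1.6.

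**Best guess**

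An observer who always guesses the arm with more places left is right for 66.6% of all allocations (enumeration of the 70 blocks), against 50% with no predictability.

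**Varying block sizes**

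I simulated an observer who knows the set of possible sizes, each equally likely, but not which is in use, and who updates after every allocation. Lists ran from 60 to 400 women:

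| Sizes | Certain | Best guess correct |
|---|---|---|
| 8 only (exact) | 20.0% | 66.6% |
| 6, 8, 10 | about 1.5–1.7% | about 66% |
| 8, 10, 12 | about 1.1–1.4% | about 65% |

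Per 100 women, certain allocations fall from about 20 to between 1 and 2. The advantage of guessing hardly changes.

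**Imbalance**

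The largest difference between arms at any moment is half the largest block: 8/2 = 4 now, and 12/2 = 6 with sizes 8, 10 and 12.

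**The case against.** The strongest reply is that the usual safeguards are in place. An uninvolved central unit holds the lists, most non-inclusion criteria are checked in the medical record, consent is signed before the arm is requested, and a daily list of eligible women with reasons for non-inclusion is kept. These stand and narrow the route to bias. They leave open the decision to approach a woman and the way consent is discussed, both of which come before the call. The daily list would help to detect differential non-inclusion but does not prevent it.

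A second reply is that 20% overstates what any one person knows. The article speaks of a research team and a team of nurses, and one centre has three rooming-in units. If several recruiters do not share allocations, each can deduce less. This stands: 20% is an upper bound.

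A third is that varying the sizes gains little, because a good guess can also drive selection and the best-guess rate barely moves. That is true, and the gain is confined to the certain allocations.

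A reader might also infer that foreknowledge would steer the exclusions for breastfeeding mechanics or the mother–child bond. The documents do not support that link. In the recruitment section these exclusions come after the description of what is done in each arm, so they appear to follow allocation, when the open researcher already knows the arm and block size is irrelevant. That is a separate question. Nor do the documents show that selection will occur.

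**Conclusion.** The point holds as a weakness in a stated design choice. For a recruiter who knows the block size and all earlier allocations at the centre, up to 20% of allocations are known in advance. This rests on four-and-four blocks (inferred), complete blocks in the long run, and full knowledge of the centre's earlier allocations. It is lower where recruiters do not share them. Central allocation and consent before the call do not remove it. The effect on the estimated duration of exclusive breastfeeding cannot be sized from the documents.

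A minor note concerns the pilot, which plans "20 participants from each center, 10 allocated in the intervention group, and 10 in the control group for each center". If the pilot uses the same blocks, 20 women fill two blocks and half of a third (8 + 8 + 4), and an exact 10:10 split has probability C(4,2)²/C(8,4) = 36/70 = 51.4% per centre. The article does not say that the pilot uses these blocks, and the furthest possible split is 12:8, so only the wording is affected.

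**What to change.** Before the main trial starts (expected in November 2023 under Clinical trial status, after the pilot), have the randomisation centre generate new per-centre lists with randomly varying block sizes, for example 8, 10 and 12. Withhold the sizes from recruiting staff and leave them out of site documents. Keep the present order of eligibility check, consent and then the call. It would also help to state how many researchers recruit at each centre and whether they see one another's allocations.

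The cost is small. The possible within-centre imbalance rises from 4 to 6. Under Ethical aspects, any modification must be documented as an amendment and communicated to the ethics committee, the registry and the journal. The public wording can say that sizes vary and are held by the randomisation centre, without listing them while recruitment is open. For the pilot, describing the split as about ten per arm per centre is enough.

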### Intervention

The non-pharmacological intervention to be tested will be breastfeeding counseling during the dyad hospitalization in the rooming-in wards, developed by a nurse trained in breastfeeding counseling. The control group will receive institutional assistance. Breastfeeding actions, in Brazil, are not systematized but focused on clinical management and health education, prioritizing binomials at high risk for weaning [23].

### Experimental group

In the intervention group, counseling will be carried out by a team of nurses qualified for breastfeeding management and counseling.

Women will be encouraged to answer the following open questions: How are you breastfeeding? Moreover, if she has doubts or concerns, they will be explored with: Tell me about it… Next, the following guiding question will be used: How are you feeling breastfeeding? Furthermore, in the end, you will be asked: What led you to breastfeed? The validated protocol for counseling on breastfeeding during hospitalization in rooming-in wards will be used for all responses.

Postpartum women allocated to this group will be approached using counseling, as described above. The researcher will collect the history of breastfeeding with the counseling approach and observe the breastfeeding. During breastfeeding, the LATCH [24] scale items will be observed—latching on, swallowing, type of nipple, comfort, and positioning. Afterward, the researcher will interview the puerperal woman and fill in sociodemographic, clinical, and obstetric data.

At the end of the first counseling session, the researcher will fill in the items of the scale adapted from the observation and evaluation form for rooming-in wards—Fantinelli’s scale [25], which measures the care complexity of the dyad.

Counseling will be offered twice a day until hospital discharge in the morning and afternoon, and the start and end times of the intervention will be recorded to determine the duration.

At the end of the intervention, the women will be invited to watch a videoscribe with the theme “Breastfeeding is better,” produced by the study group, in which the advantages of breastfeeding for the mother and newborn are discussed and guidance is given to seek help in case of breast complications. The video has three distinct versions, with the voices of the researchers of each center and a version in Brazilian Sign Language. The version adapted to the participant’s location will be used. The Brazilian Sign Language version was created for inclusion and health education purposes for these women but will not be used in this study.

The intervention (implementing individualized counseling on the duration of exclusive breastfeeding) will not require alteration to usual care pathways, including use of any medication for postpartum woman or neonates and these will continue for both trial arms.

After hospital discharge, telephone contacts will be made through the number provided by the participant to collect the outcomes. To ensure that there is no loss of contact, the researcher will request the contact of the postpartum woman and a family member at the time of allocation. Contact will be made by the researcher who collected the data with the postpartum women included to maintain the link with the postpartum women and reduce sample losses. Contacts will be made: in the first and second weeks of life, with 1, 4, and 6 months of the child’s life to collect the outcomes.

It should be noted that all researchers at the participating centers are not part of the care teams at the units. All were trained to intervene with the Clinical Management of Breastfeeding course (60 h) and Counseling Workshop (16 h), including practical activities, totaling 76 h of training.

### Control group

The control group will receive standard institutional care, that is, the assistance offered by a professional, from the institution itself, without intervention by the researchers.

In these cases, the researcher responsible for data collection will conduct the interview and non-participant observation of at least one feeding without applying any intervention. The same instruments used in evaluating the intervention group will be applied. At the end of the interview, participants will also be invited to watch the videoscribe produced for the study.

Telephone contacts will be made, as well as in the intervention group, in the first and second weeks of life, with 1, 4, and 6 months of the child’s life to collect the outcomes.

### Criteria for discontinuing the intervention

Interim analyses will be performed every 60 days during data collection and presented to a clinical trial safety monitoring committee to assess the continuity of data collection, given the findings of adverse events or statistical differences between the groups surveyed concerning primary and secondary outcomes. The data analysis will be of the type by the finalization of the protocol, denominated explanatory.

This committee is highly recommended for RCTs being utilized by the FDA and NIH. It is suggested that in its minimum composition, it has a specialist in the subject, a specialist in RCT, a specialist in statistics/epidemiological studies, a representative of the Ethics Committee, and a representative of the users (who are in the same condition as the study participants) [26]. The proposed committee for this study will consist of five representatives, two specialists in the subject and in conducting RCTs, one specialist in epidemiological studies and statistics, a representative of the Ethics Committee, and a representative of the users. The participants of this committee will not be involved in the study team and have indicated that they are aware of this condition.

The study must be stopped if there is definitive evidence, during its conduction, of the benefit or lack of benefit of the intervention, which the specific Monitoring Committee will evaluate for this randomized clinical trial [26].

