### Safety protocols

All biosecurity protocols will be strictly followed, and the data collection team will use all necessary personal protective equipment.

As for adverse events, their occurrence is not predictable in this research, given the nature of the intervention. However, in case of any complication or adverse event for the participants, the information will be registered, and the Research Ethics Committee will be immediately communicated.

It should be noted that the study will be stopped if there is definitive evidence, during its conduction, of the benefit or absence of benefit from the intervention, which the specific Monitoring Committee will evaluate for this randomized clinical trial.

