### Clinical trial status

The study protocol’s final version (version 1) occurred on January 9, 2022. Recruitment of participants for the pilot study began on March 1, 2023, and is estimated to be completed by July, 2023. The clinical trial is expected to start collection in November 2023 and estimate the end of recruitment in January 2024 and completion of the study in May 2024.

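### The stopping decision covers data collection and the whole study, although counselling ends at discharge; once recruitment has closed, a stop spares no one and truncates follow-up

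*Protocol article*

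**What the plan says.** Three parts of the protocol article bear on this.

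**What is decided.** Under *Criteria for discontinuing the intervention*: "Interim analyses will be performed every 60 days during data collection". The results are "presented to a clinical trial safety monitoring committee to assess the continuity of data collection". Two triggers are named: adverse events, and group differences in any primary or secondary outcome. The same section adds: "The study must be stopped if there is definitive evidence, during its conduction, of the benefit or lack of benefit of the intervention". *Safety protocols* repeats it: "the study will be stopped if there is definitive evidence, during its conduction, of the benefit or absence of benefit from the intervention".

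**When exposure ends.** Under *Experimental group*: "Counseling will be offered twice a day until hospital discharge in the morning and afternoon". The same section says that the calls after discharge (weeks 1 and 2, months 1, 4 and 6) serve to collect outcomes. *Data collection instruments* says that neither group receives an intervention at the week 1 and week 2 calls.

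**Dates.** *Clinical trial status* expects collection to start in November 2023, gives "estimate the end of recruitment in January 2024", and puts completion in May 2024.

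The article does not separate closing recruitment from ending follow-up. It does not say whether women already randomised are followed to month 6 after a stop.

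**The concern.** The heading of the section speaks of discontinuing the intervention, but the text beneath it discontinues data collection and the study. In a trial of long-term treatment the two largely coincide. Here they do not: a discharged woman has already received all the counselling she will get, and only her outcome calls remain to be stopped.

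Once recruitment has closed and the last women have gone home, a stop can therefore act only on follow-up. At stake are the primary outcome, the duration of exclusive breastfeeding, in women who have not yet ended it, and all the month-6 secondary outcomes. An early difference could then be neither confirmed nor seen to fade. The error rate of repeated looks is a separate matter: properly adjusted boundaries would still stop the wrong thing.

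**Working it through.** The protocol gives no number of looks and no sample size, so there is no stated figure to reproduce. The check is calendar arithmetic.

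**Inputs from the article:** looks every 60 days; collection starting in November 2023; recruitment ending in January 2024; completion in May 2024; calls at months 1, 4 and 6.

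**Assumptions:** uniform accrual from 1 November 2023 to 31 January 2024, so R = 91 days; first look 60 days after the start; 1, 4 and 6 months taken as 30, 122 and 183 days; follow-up counted from enrolment.

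**Formulas.** Look k falls on day t = 60k.
- Share enrolled = min(1, t/R).
- Share of all women past m days, limited to the range 0 to 1 = (t − m)/R.

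| Look | Date | Recruitment | Enrolled | Past month 4 | Past month 6 |
|---|---|---|---|---|---|
| 1 | 31 Dec 2023 | open | 60/91 = 66% | 0% | 0% |
| 2 | 29 Feb 2024 | closed | 100% | 120 − 122 < 0, so 0% | 0% |
| 3 | 29 Apr 2024 | closed | 100% | (180 − 122)/91 = 58/91 = 64% | 180 − 183 < 0, so 0% |

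The next look, 28 June 2024, falls after the stated completion and is not counted.

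**Varying the days within the stated months:**

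| Start to end of recruitment | Look 1 | Enrolled at look 1 | Look 2 | Look 3 | Past month 4 at look 3 |
|---|---|---|---|---|---|
| 1 Nov to 31 Jan | 31 Dec | 60/91 = 66% | 29 Feb | 29 Apr | 58/91 = 64% |
| 1 Nov to 1 Jan | 31 Dec | 60/61 = 98% | 29 Feb | 29 Apr | 58/61 = 95% |
| 30 Nov to 31 Jan | 29 Jan | 60/62 = 97% | 29 Mar | 28 May | 58/62 = 94% |
| 15 Nov to 15 Jan | 14 Jan | 60/61 = 98% | 14 Mar | 13 May | 58/61 = 95% |

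In all four cases only look 1 falls within recruitment, and month 6 stands at 0% at every one of the three looks. The month-6 result does not depend on the calendar: look 3 is always day 180, three days before the first woman reaches 183. Counting from birth instead moves this by only the infant's age at enrolment.

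**What a stop would cost.** At look 2, the last completed call is month 1 for (120 − 30)/91 = 99% of women. At look 3 it is month 4 for 64% and month 1 for the other 36%. Women who reported the end of exclusive breastfeeding by their last call have a known duration; the rest are truncated at that call. The documents give no distribution of durations, so the truncated share cannot be derived. Purely as illustration, if the Brazilian prevalence cited in the *Discussion* (45.8%) were the share still exclusive at the last call, 45.8% would be truncated and 54.2% would keep a known value.

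**What the analysis would do with them.** The article plans an explanatory analysis by finalization of the protocol, and *Data collection instruments* places its conclusion in the sixth month. If that means women who complete the protocol, truncated women drop out. *Statistical analysis* names the t test and Mann–Whitney for numeric variables and no method for censored durations.

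**The case against.** **The ward-stage reading.** Data collection could mean the hospital stage only. The figure list separates the data-collection procedure from follow-up after discharge, the *Control group* section uses the term for the ward interview, and the section heading speaks of the intervention. On that reading the committee decides on enrolment and counselling, and looks end with recruitment. This deserves weight, but it does not carry. The looks concern primary and secondary outcomes, most of which come from the calls, and the calls are described under both headings that contain the words data collection. The stopping sentences also refer to the study as a whole.

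**Silence in a condensed article.** No sentence says that calls cease after a stop, and such detail often sits in the full protocol. That is fair as far as it goes: a reader might infer that the article orders follow-up to end, and it does not say so expressly. But it does fix what the decision is about, and a committee following that wording could end the calls.

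**A high threshold.** Stopping needs definitive evidence judged by an independent committee, and with nobody at month 6 such evidence on the primary outcome is unlikely. This lowers the probability of the problem. It does not remove it: secondary outcomes also count, and those of the first two weeks are complete by look 2, when the last woman is 120 − 91 = 29 days past enrolment.

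**Provisional dates.** They were set before the sample size, so the percentages are illustrative. This stands.

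**Conclusion.** The point holds and should be corrected before the trial starts. On the protocol's own dates, two of the three looks before the stated completion fall when stopping can no longer change anyone's exposure and no woman has a month-6 contact. A stop then truncates durations still running and loses the month-6 outcomes, under an analysis plan that offers truncated women no clear place. This rests on uniform accrual, on the provisional dates and on reading data collection to include the calls.

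Stronger conclusions that a reader might draw are not supported:
- **The primary outcome would be lost altogether.** It is a duration, so women already recorded as having ended exclusive breastfeeding keep a known value.
- **No stop can spare anyone.** At look 1, 2% to 34% of women are still to be enrolled across the four date scenarios (100% less 98% and 66%).
- **Benefit and lack-of-benefit decisions must be dropped after recruitment closes.** That is a design preference, not the repair of a contradiction.

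**What to change.** Reconcile *Experimental group*, *Criteria for discontinuing the intervention* and *Safety protocols*. Two sentences would do: an early-stopping decision on benefit or lack of benefit closes recruitment; every woman already randomised continues the planned calls to month 6 and is included in the analysis. The statement about analysis by finalization of the protocol should be worded to agree with the second sentence.

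The change concerns recruitment and follow-up only. What happens to counselling for women still in hospital at a stop, or after an adverse-event signal, is for the investigators to state.

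The cost is completing telephone calls that are already planned. A woman enrolled on 31 January 2024 reaches day 183 on 1 August 2024, so the May 2024 completion date has to be reconciled as well. That conflict exists with or without an early stop.
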